### Eligibility criteria

#### Inclusion criteria

Eligible patients are men or women aged 18–70 years with a pre-existing headache disorder onset at or before age 50, fulfilling the ICHD-3 diagnostic criteria for MOH (coded as 8.2) (35) with ≥15 headache days per month and with regular overuse of acute pain medications ≥ 10 or 15 days per month depending on the medication type for ≥ 3 months.

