### Outcome measures

As there is a lack of guidelines for reporting results from clinical trials on MOH, we will adopt Hagen et al.'s suggestion on endpoints for MOH studies in follow-up including headache days/month, acute medication use days/month, headache intensity, cured MOH, and responder rate (37).

Primary efficacy endpoint is reduction in the mean number of monthly headache days from baseline at 24-week follow-up.

Secondary efficacy endpoints include:

a. Headache intensity at 12 and 24-week follow-up. The headache intensity at each headache onset will be measured on a 4-point scale (0 = pain, 1 = mild pain, 2 = moderate pain, 3 = severe pain), and be calculated as the average of headache intensity at each headache onset for 1 month;b. Proportion of cured MOH, defined as a patient does not fulfill the diagnostic criteria for MOH in ICHD-3 at 12 and 24-week follow-up;c. Mean change from baseline in total HIT-6 score and the proportion of patients with a ≥ 5-point reduction in total HIT-6 score (38) at 12 and 24-week follow-up. For total HIT-6 scores, a between-treatment group minimally important difference (MID) has been established as ≥2.3 (39). Additionally, a clinically meaningful change for an individual patient has been defined as a ≥ 5-point decrease in total HIT-6 score;d. 50% responder rate, defined as 50% reduction of from baseline in number of moderate or severe headache days at 12- and 24-week follow-up;e. Treatment failure, defined as use of acute medication intake >2 days per week during 12-week treatment;f. Reduction in the mean number of monthly medication intake days for treatment failures at 12- and 24-week follow-up;g. Quality of life (QoL), as measure by the Short Form 36-Item Health Survey (SF-36) (40) at 12- and 24-week follow-up.

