### Sample size

We will estimate each of the above mentioned variables to calculate endpoints for MOH studies according to a published study (22). Hypothesis test will be 2-tailed with 90% power and a significance level of *P* < 0.05. Sample size estimations for the four recommended endpoints are provided in Table 2.

**Table 2 T2:** Sample sizes estimation for each critical endpoint.

**Endpoints**	**Target power**	**Alpha**	**N1**	**N2**	**N**	**Assumed proportion (or mean) for treatment group**	**Referred proportion (or mean ±SD) for control group^*^**	**Difference between groups**
Reduction in monthly headache days	90%	0.05	77	77	154	46%	22%	24%
Cured medication overuse headache	90%	0.05	44	44	88	90%	62%	28%
Headache intensity	90%	0.05	22	22	44	20.7	38.4 ± 17.4	17.7

* Data referred for sample size estimation are all obtained from a published study (reference 16) which enrolled patients with medication overused headache who were assigned to restricted acute medication intake group (allowing to take up to 2 days a week with analgesics or migraine medication during the study period).

Finally, we assume group sample sizes of 77 in gastrodin group and 77 in the control group will achieve 90.188% power to detect a difference between the group proportions of 24%. The proportion in the gastrodin group is assumed to be 22% under the null hypothesis and 46% under the alternative hypothesis. The proportion in control group is 22% based on previously published literature (22). The test statistic used is the two-sided *Z*-Test with unpooled variance. To allow for 20% dropouts, we will include 186 patients, corresponding to 93 in each group.

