## Methods: Assignment of interventions

### Allocation

#### Sequence generation

The external block randomization process will take place at Yunnan University. The project statistician will create a randomized treatment allocation schedule using SPSS by generating 186 numbers. Patients who fulfill criteria for enrollment will be randomly assigned to receive gastrodin or placebo according to a centralized randomization schedule in blocks of 4, stratified by gender and headache frequency at baseline (<14 vs. >14 days per month), to achieve between-group balance in the baseline. Subjects will be assigned to the next available medication number within the block.

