### Statistical methods

All analyses on efficacy endpoints will be performed using the intention-to-treat (43) principle which includes all randomized patients who had an evaluable baseline period of eDiary data (week-0), received at least 1 dose of gastrodin or placebo, and had at least one evaluable follow-up appointment. Safety evaluations will be performed consisting of all participants who received at least 1 dose of study intervention.

Continuous variables are presented as mean ± standard deviation (44) conforming to the normal distribution and median (interquartile range; IQR) for the skew distribution data. Student's *t*-test and Mann-Whitney *U*-test will be used to test differences in continuous variables where appropriate. Categorical variables will be expressed by the number and percentage of occurrences. Differences between two groups will be compared using chi-squared tests or Fisher's exact test where appropriate.

Cox proportional hazard regression (backward stepwise method) analysis and the Kaplan-Meier survival curve will be performed when necessary.

To more completely understand the clinical meaningfulness of the new therapy for MOH results from different headache type, we will conduct a subgroup analysis based on prior headache type (CM/CTTH or CM/ other types of headaches) for all the efficacy endpoints.

Participants who do not complete or are lost to follow-up will be coded as treatment failure, missing values will be handled using multiple imputation method under the missing-at-random (MAR) assumption (45).

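### For the primary change in headache days the protocol states only an unadjusted t-test or Mann-Whitney test chosen by distribution; one baseline-adjusted model should be prespecified

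*Protocol article*

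**What the plan says.** The Outcome measures section makes the primary endpoint a continuous change score: "Primary efficacy endpoint is reduction in the mean number of monthly headache days from baseline at 24-week follow-up".

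The Statistical methods section gives one general rule for continuous data. Summaries are the mean and standard deviation for data "conforming to the normal distribution and median (interquartile range; IQR) for the skew distribution data". The t-test and the Mann-Whitney test then "will be used to test differences in continuous variables where appropriate". The section names no analysis of covariance, mixed model, baseline covariate or stratified test. The only regression is a Cox model, to be used if needed. Missing values are to be handled by multiple imputation under missing at random.

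The Sequence generation section says that randomisation is "stratified by gender and headache frequency at baseline (<14 vs. >14 days per month), to achieve between-group balance in the baseline". The Inclusion criteria admit only patients "with ≥15 headache days per month".

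The Sample size section sizes the primary endpoint as a comparison of two proportions, 46% against 22%, by a two-sided Z-test with unpooled variance at 90% power.

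**The concern.** The stated method is weaker than one that the trial could use at no cost, in three respects.

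- **Precision.** Subtracting the baseline fixes its coefficient at 1. ANCOVA estimates the coefficient, and its variance is no larger than that of the change score, apart from one degree of freedom.
- **Design and analysis.** Randomisation is stratified, but no stratification factor enters the stated analysis. If gender is prognostic, the unadjusted standard error tends to be too large.
- **Target of the analysis.** The t-test addresses the mean difference that the endpoint describes; the Mann-Whitney test is a rank comparison and does not estimate it. Standard pooling over imputed datasets needs an estimate and a standard error from each one, and the rank test gives no mean difference to pool. Headache days are bounded and eligibility cuts the baseline at 15, so skewed data are plausible and the rank test may well be chosen. The protocol gives no explicit criterion for that choice.

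At stake are some precision and a clear statement of what the primary result will estimate.

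**Working it through.** **1. The plan's own figure.** The inputs from the Sample size section are proportions of 46% and 22%, two-sided alpha 0.05 and 90% power.

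n = (1.960 + 1.2816)² × (0.46×0.54 + 0.22×0.78) / 0.24² = 76.6, rounded up to 77 per arm.

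Power at 77 is 90.14%; the protocol states 90.188%. The figure reproduces. It belongs to a test of proportions, however, so it does not show the power of a t-test or a Mann-Whitney test on headache days.

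**2. Which stratification factors vary.** The frequency strata are below 14 and above 14 days per month, and eligibility requires at least 15. Every patient falls in the upper stratum, so only gender varies. Its prognostic value is not given.

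**3. Change score against ANCOVA.** Let SD_b and SD_f be the standard deviations at baseline and week 24, and r their correlation.

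- Variance of the change score: SD_b² + SD_f² − 2·r·SD_b·SD_f
- Residual variance of ANCOVA: SD_f²·(1 − r²)
- Difference: (SD_b − r·SD_f)², which is never negative

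With equal SDs the variance ratio reduces to (1 + r)/2. The protocol gives no SD of headache days and no correlation, so the rows below are assumptions. The last column takes a change-score t-test with 90% power and computes Φ(3.2415/√(1 − saving) − 1.960).

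| Assumed SD_b, SD_f | r | Change variance | Excess | Saving | 90% power becomes |
|---|---|---|---|---|---|
| equal (5, 5) | 0.3 | 35.0 | 12.25 | 35% | 98.0% |
| equal (5, 5) | 0.6 | 20.0 | 4.00 | 20% | 95.2% |
| 4, 5 | 0.3 | 29.0 | 6.25 | 22% | 95.5% |
| 4, 5 | 0.6 | 17.0 | 1.00 | 6% | 91.6% |
| 4, 7 | 0.3 | 48.2 | 3.61 | 7% | 92.1% |
| 4, 7 | 0.6 | 31.4 | 0.04 | 0.1% | 90.0% |

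The lower rows are at least as plausible as the upper ones. Eligibility confines baseline to 15 days or more, whereas week 24 can range down to zero, so SD_b is likely to be the smaller.

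**4. Simulation with truncated baseline.** Assumptions: baseline uniform on 15 to 28 days, residual SD 6.5, effect 3.5 days, 77 per arm, 6,000 replicates.

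| Slope on baseline | t-test on change | ANCOVA | Gain |
|---|---|---|---|
| 0.5 | 88.0% | 91.0% | 3.0 points |
| 0.8 | 90.2% | 90.8% | 0.6 points |

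**5. Choosing the test by a normality check.** In the same simulation under no effect, picking the t-test or the Mann-Whitney test by a Shapiro-Wilk check in each arm gave type I error of 4.7% and 5.3%.

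**The case against.** The case on the other side has real weight.

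- **No test is assigned to the primary endpoint by name.** The rule is a general sentence, and the Sample size section uses a different test again. This stands, and the point is worded accordingly. Even so, no other stated method fits a continuous endpoint.
- **Covariates and pooling are usually settled in an analysis plan that is not shown.** That would excuse silence. Here the article states a method, and what is criticised is the stated method.
- **The change-score test is valid in a randomised trial.** This stands. The issue is precision, not bias. A reader might infer that baseline is ignored; it is not, because it is subtracted.
- **The 20 to 35% saving depends on equal SDs.** This stands. It is the favourable end of the range.
- **Only one stratification factor is lost.** This stands. A reader might infer that two are, but the lower frequency stratum is empty.
- **Data-driven choice of test.** A reader might infer an inflated false-positive rate. The simulation shows none, and the Blinding section keeps the statistician blinded until the analyses are finished.
- **Visits at weeks 4, 8 and 12.** A reader might infer that these data are wasted. The imputation model is not described and may use them, and a single-timepoint primary endpoint is legitimate.
- **The Mann-Whitney problem arises only if that test is chosen.** True, but the protocol leaves it open.

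**Conclusion.** The concern holds as a matter of efficiency and of a primary analysis that is not fixed. The only stated methods for a continuous efficacy outcome are two unadjusted tests chosen by distribution. One of them does not estimate the mean difference and does not pool in the standard way over imputations; that part rests on no assumed correlation.

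The size of the precision gain is not known. It rests on SDs and a correlation that the protocol does not give. Over the ranges assumed here the variance saving is 0.1% to 35%, and in the truncated-baseline simulations the gain was about 1 to 3 power points. The protocol states no power for a t-test on headache days, so no actual power loss can be quoted. The documents support neither a claim of bias nor one of type I error inflation.

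The change is worth making because it is free, but the trial's validity does not depend on it.

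**What to change.** Prespecify one primary analysis before unblinding: an ANCOVA of week-24 monthly headache days on treatment, continuous baseline headache days and gender. Report the adjusted mean difference with its 95% confidence interval, combined over the imputed datasets. Keep the rank test as a sensitivity analysis. State by name that this model is the test of the primary endpoint, and bring the sample size justification into line with a continuous endpoint.

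The cost is one sentence of analysis wording, plus the alignment of the sample size text. Baseline headache days are already collected and gender is already used for stratification, so no extra patients, visits or data are needed.

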### Safety measures

All subjective adverse events (41) will be collected from the time of allocation through the last visit (week 24). The investigators are responsible for assessment of the severity and causal relationship of all AEs to study intervention. Documentation on start date and duration of AE, treatment measures taken for the AE will be recorded.

Tolerability will be assessed by proportion of drop-outs due to AEs throughout double-blind period, with lower dropout rates indicate higher tolerability.

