## Methods: Data collection, management, and analysis

### Data collection methods

Baseline survey and efficacy assessments will be based on information recorded by participants using an eDiary mobile application. Baseline information includes age, educational level (years), any medical history, family history of headache, body mass index, age of headache onset, pre-exiting headache type, monthly headache days, and month medication intake days.

Following variables will be recorded both at baseline survey and each headache attack after randomization: headache characteristics, headache associated symptoms, the headache pain intensity, pain duration of an attack (hours), and acute medication use (type and dosage).

Monthly headache days, month medication intake days, the headache pain intensity, score of HIT-6 and SF-36, treatment failure, drop-outs and any adverse events will be assessed at 4, 8, 12, and 24-week follow-up.

A summary table of eDiary is shown in Table 3. Training for the eDiary will be provided for qualified participants during before randomization.

**Table 3 T3:** Summary of data collection from eDiary.

**Variables recorded**	**Day-28–0**	**At each headache onset after randomization**			
Age	x				
Body mass index	x				
Education years	x				
Age of first headache onset	x				
Any medical history	x				
Family history of headache	x				
Diagnosis of pre-existing headache	x				
Monthly headache days	x				
Month medication intake days	x				
Headache pain characteristics	x	x	x	x	x
Headache associated symptoms	x	x	x	x	x
Headache intensity	x	x	x	x	x
Duration of headache pain (hours)	x	x	x	x	x
Type of acute pain medication intake	x	x	x	x	x
Dosage of acute pain medication intake	x	x	x	x	x

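### A backward stepwise Cox model is to be run as the need arises, with no time-to-event endpoint defined; if treatment can be eliminated, its hazard ratio is selected on significance

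*Protocol article*

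**What the plan says.** The sentence at issue is in the Statistical methods section of the protocol article: "Cox proportional hazard regression (backward stepwise method) analysis and the Kaplan-Meier survival curve will be performed when necessary". It fixes a selection method (backward elimination) and a trigger (perceived need), and attaches neither to an endpoint.

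The endpoints are of other kinds:

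- Primary (Outcome measures): "Primary efficacy endpoint is reduction in the mean number of monthly headache days from baseline at 24-week follow-up". This is a change in a count at a fixed time.
- Secondary endpoint e, treatment failure, comes closest to an event: "use of acute medication intake >2 days per week during 12-week treatment". It is a status over a window.
- Tolerability (Safety measures): "Tolerability will be assessed by proportion of drop-outs due to AEs throughout double-blind period". This is a proportion.
- The other secondary endpoints are scores, changes and proportions at 12 and 24 weeks.

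Statistical methods already gives these endpoints their tests. For categorical variables, "Differences between two groups will be compared using chi-squared tests or Fisher's exact test where appropriate". For continuous variables, the t-test and the Mann-Whitney test "will be used to test differences in continuous variables where appropriate". Data collection methods adds that "treatment failure, drop-outs and any adverse events will be assessed at 4, 8, 12, and 24-week follow-up".

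**The concern.** Two features of the sentence sit badly in a randomised comparison.

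First, the trigger. An analysis that serves no declared endpoint and is run when someone judges it needed is an extra comparison, and the decision to run it can follow a look at the data.

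Second, the selection method. Backward elimination lets the data decide which terms stay. If the treatment term is among the candidates, it is reported only when its p-value survives. Conditional on survival, the estimate is too far from 1, and its interval ignores the selection.

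This is more than a detail left to a fuller document. The article states the method and the trigger. An analysis plan that followed it would inherit both, and one that did not would contradict it.

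**Working it through.** **The plan's own figures.** The article gives no event count, hazard ratio, removal threshold or power for a Cox analysis, so there is nothing to reproduce on this point. The sample-size power does not involve the Cox model. With 46% versus 22% and 77 per group, the unpooled Z-test gives 0.24 / √((0.46×0.54 + 0.22×0.78)/77) − 1.96 = 3.25 − 1.96 = 1.29, or 90.14%, against the stated 90.188%.

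**Assumptions for the Cox check (none is in the documents).** Treatment is removable; removal is at two-sided p > 0.10; there are D = 60 events (range 30 to 90); the true HR runs from 1.0 to 0.5.

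**Formula.** With 1:1 allocation the estimated log HR is approximately normal, with mean log(HR) and standard error 2/√D. The z statistic therefore has mean μ = log(HR)·√D/2 and variance 1, and treatment is kept if |z| > 1.645.

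- P(kept) = Φ(−1.645 − μ) + 1 − Φ(1.645 − μ).
- The mean reported HR is the exponential of the mean log HR among kept trials.

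**Example, true HR 0.80, D = 60.** The standard error is 2/√60 = 0.258 and μ = −0.223 × 3.873 = −0.86. Then P(kept) = Φ(−0.78) + 1 − Φ(2.51) = 0.217 + 0.006 = 22.3%.

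**Results with 60 events (2,000,000 draws per row).**

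| True HR | μ | Kept | Favourable | Unfavourable | Mean reported HR if kept |
|---|---|---|---|---|---|
| 1.00 | 0 | 10.0% | 5.0% | 5.0% | 1.00 (0.59 among the favourable) |
| 0.80 | −0.86 | 22.3% | 21.7% | 0.6% | 0.58 |
| 0.70 | −1.38 | 39.7% | 39.6% | 0.1% | 0.55 |
| 0.50 | −2.68 | 85.1% | 85.1% | 0.0% | 0.47 |

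The mean absolute log HR among kept trials is 2.6, 1.7 and 1.1 times the truth at HR 0.80, 0.70 and 0.50.

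**Range over 30 to 90 events.**

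- True HR 0.80: kept in 16% to 28%, mean HR 0.51 to 0.63.
- True HR 0.70: kept in 26% to 52%, mean HR 0.45 to 0.60.
- True HR 0.50: kept in 60% to 95%, mean HR 0.40 to 0.49.

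**Check by simulating the elimination itself.** Cox models were fitted to 154 patients with treatment and seven covariates, a control event risk of about 38% and removal at p > 0.10.

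- True HR 1.0 (400 runs, about 60 events): removable treatment was kept in 10.75% (6% favourable, 4.75% unfavourable). With treatment forced in, the mean HR was 1.01.
- True HR 0.70 (150 runs, about 53 events): removable treatment was kept in 36% with mean HR 0.51. With treatment forced in, the mean HR was 0.69.

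Selecting covariates around a retained treatment term produced no exaggeration in this check.

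**The case against.** A reader might infer that a treatment hazard ratio will appear only when the data favour gastrodin, and will then be exaggerated. The article does not support that, for three reasons, all of which stand.

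- It does not say that treatment is a removable candidate, or even that the Cox model compares the treatments. The sentence is compatible with choosing covariates around a retained treatment term, or with exploratory prognostic modelling.
- Elimination by p-value is two-sided. With no effect, unfavourable hazard ratios survive as often as favourable ones. One-sided reporting would also need selective use of the trigger. The Blinding section keeps the statistician blinded until the analyses are finished, which limits choosing by direction, though not choosing on whether the coded groups differ.
- The size depends on assumed inputs. The plan expects large effects (46% versus 22%, and 90% versus 62% in the sample-size table), and the bias is small when the true hazard ratio is far from 1.

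It can also be said that survival methods are usable here. Treatment failure and drop-out happen within a follow-up window, and acute medication use is recorded at each headache onset, so event times could be derived. That is fair. A condensed article may also leave the event, origin, censoring and candidate covariates to the full protocol, and their absence is not held against it. What remains is what the article does state: a stepwise method and an open trigger, tied to no endpoint.

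**Conclusion.** The point holds in a limited form. The article commits to a data-driven Cox model with a discretionary trigger and no defined time-to-event endpoint, so its use and content can be decided after the data are seen. That part needs no assumption.

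Bias in the treatment hazard ratio is conditional on treatment being subject to elimination. It is then substantial for modest effects (true 0.80 reported on average as 0.58 with about 60 events and removal at p > 0.10) and slight for large ones (0.50 reported as 0.47). It is absent if treatment is forced in.

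The article gives the Cox model no confirmatory role, and the primary endpoint, its tests and the sample size do not depend on it. This is a worthwhile tidying of the text, not a threat to the main result.

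**What to change.** Delete the sentence. Alternatively, replace it with one supportive analysis, labelled exploratory:

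- **Endpoint:** time from randomisation to first treatment failure (endpoint e) within 12 weeks, with the event dated from the eDiary.
- **Drop-outs:** one stated rule. Statistical methods currently codes non-completers as failures and also imputes missing values, and neither is a censoring rule for a survival model.
- **Analysis:** a Kaplan-Meier curve and one Cox model that always retains treatment, gender and baseline monthly headache days as a continuous variable, with no stepwise selection.

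The headache-frequency stratum should not be the covariate. Sequence generation splits it at below versus above 14 days per month, while the inclusion criteria require at least 15, so it does not vary among eligible patients.

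The change is one sentence and needs no new data. The only loss is analyst discretion.

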## Introduction

### Background and rationale

Medication overuse headache generally refers to monthly headache days of ≥15 per month resulting from acute “medication overuse” (MO) defined as the frequent consumption of acute pain medications above a certain threshold (e.g., 10 or 15 days per month depending on the medication type) for ≥3 months. Diagnostic criteria for MOH were introduced in the International Classification of Headache Disorders, 2nd edition (ICHD-2) (1) without a the requirement of the diagnosis of chronic migraine (CM; see Appendix for details on MOH and CM). In the third edition beta version (ICHD-3β), updated in 2013, concurrent CM and MOH are diagnosed if both criteria are met (2). These criteria remain the same in the ICHD-3 criteria.

The prevalence of MOH is still uncertain (3) and varies from 2% in a recent population-based study (4) to 60% in the Global Burden of Disease Study (5). Whether MOH is a cause or consequence of frequent acute medication intake has been debated for years (6, 7). Nonetheless, MO and MOH management are important in clinical care. MO is associated with an increased risk of chronic headache (8) and chronic migraine (9, 10).

Prognosis of MOH due to different type of chronic headache is probably variable. Although there is evidence that chronic tension-type headache (CTTH) and CM may have partly distinct pathophysiological mechanisms, clinical experience suggests that these two clinical entities may be at opposite poles of a single disease spectrum (11, 12). Of note, CM with MO represents a more severe subgroup of patients and can be difficult to treat (13). In a preplanned subgroup analysis that evaluated efficacy and safety of erenumab in patients with CM and MO, the medication overuse subgroup had a higher proportion of failing to respond to preventive treatment (14).

Effective education for people with MOH plays a major role in effective withdrawal therapy. Successful educational interventions rely largely on a productive doctor-patient alliance (15) and patients' motivation for adherence. In addition, it is often recommended to add a preventive therapy or optimize existing preventive regimens to reduce the number of monthly headache days, improve sense of self efficacy and as a result reduce both the physical and psychological need for acute medication for migraine. Preventive treatments may be pharmacologic, non-pharmacologic, or both.

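### The headache-type subgroup analysis names two alternative splits instead of one, and the two-group tests listed cannot show whether the effect differs by type (minor)

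*Protocol article*

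**What the plan says.** The Statistical methods section of the protocol article gives the subgroup analysis one sentence. Its purpose is stated as "To more completely understand the clinical meaningfulness of the new therapy for MOH results from different headache type", and its content as a "subgroup analysis based on prior headache type (CM/CTTH or CM/ other types of headaches) for all the efficacy endpoints". The introduction supplies the motive: "Prognosis of MOH due to different type of chronic headache is probably variable".

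For comparing groups, the section names Student's t-test and the Mann-Whitney U-test for continuous variables. For categorical ones, "Differences between two groups will be compared using chi-squared tests or Fisher's exact test where appropriate". It also mentions backward stepwise Cox regression and Kaplan-Meier curves, to be used when necessary and not tied to the subgroups.

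The 0.05 level appears only under Sample size. No level, reading rule or subgroup size is given for the headache-type analysis. Randomisation is stratified by gender and headache frequency, not by headache type (Sequence generation).

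**The concern.** Two things in the sentence are stated in a way that does not work.

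First, the grouping does not yield one set of subgroups. CM against CTTH and CM against every other type cover different patients. The inclusion criteria admit a pre-existing headache disorder without restricting its type, so the first split leaves out anyone whose prior headache is neither CM nor CTTH, and the second keeps them. Whoever runs the analysis has a choice of split for each efficacy endpoint, and nothing in the article says it must be made before results are available.

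Second, the purpose is to learn how results vary by headache type. That is a question about a difference between two treatment effects. A two-group test within CM and another within CTTH each ask whether there is an effect in that type. Neither asks whether the two effects differ. Setting the two P values side by side is a poor substitute, because each rests on a fraction of the sample and they will often disagree by chance alone.

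At stake is the reading of a secondary analysis: an apparent contrast between headache types could be taken for a real one, or the more striking of two splits could be the one reported.

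**Working it through.** **Inputs.** From Sample size: "Hypothesis test will be 2-tailed with 90% power and a significance level of" 0.05; rates of 22% and 46% ("The proportion in the gastrodin group is assumed to be 22% under the null hypothesis and 46% under the alternative hypothesis"); "group sample sizes of 77 in gastrodin group and 77 in the control group will achieve 90.188% power"; the test is a two-sided Z-"Test with unpooled variance". The share of patients in each headache type is not given, so it is assumed at 50:50 and 70:30, with 80:20 as a more extreme case.

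**The plan's own figure.** Variance sum: 0.46 × 0.54 + 0.22 × 0.78 = 0.2484 + 0.1716 = 0.42.
- n per arm = (1.960 + 1.282)² × 0.42 / 0.24² = 76.6, so 77.
- At 77 per arm, SE = √(0.42/77) = 0.0739, 0.24/SE = 3.25, and power = Φ(3.25 − 1.96) = 90.1%. The stated 90.188% is reproduced closely enough.

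**Power within each type when the true effect is the same in both.** With a share f of patients in a type, n per arm is 77f, and power = Φ(0.24/√(0.42/77f) − 1.96).
- 50:50 (38.5 per arm in each type): Φ(2.298 − 1.960) = 63.2% in each.
- 70:30 (53.9 and 23.1 per arm): Φ(2.719 − 1.960) = 77.6% and Φ(1.780 − 1.960) = 42.9%.
- 80:20 (61.6 and 15.4 per arm): 82.8% and 30.6%.

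**Chance that exactly one type is significant.** The types contain different patients, so the tests are independent: P = a(1 − b) + b(1 − a).
- 50:50: 2 × 0.632 × 0.368 = 46.5%, about 47%.
- 70:30: 0.776 × 0.571 + 0.429 × 0.224 = 53.9%, about 54%.
- 80:20: 0.828 × 0.694 + 0.306 × 0.172 = 62.7%.

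With no effect in either type, the same event has probability 2 × 0.05 × 0.95 = 9.5% per endpoint.

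**What an interaction test could detect.** Suppose the effect is 24 points in one type (the larger, if unequal) and 0 in the other, where both arms have a 22% rate. The variance of the difference in effects is 0.42/n₁ + 2(0.22 × 0.78)/n₂ = 0.42/n₁ + 0.3432/n₂.
- 50:50: SE = √(0.42/38.5 + 0.3432/38.5) = 0.1408; power = Φ(0.24/0.1408 − 1.96) = 39.9%.
- 70:30: SE = √(0.42/53.9 + 0.3432/23.1) = 0.1505; power = Φ(0.24/0.1505 − 1.96) = 35.7%.

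**Limit of the calculation.** The 90% power refers to a difference in proportions, whereas the Outcome measures section defines the primary endpoint as a reduction in mean monthly headache days. The discordance figures depend only on the overall power and the split, so they carry over to any endpoint powered at about 90%. The interaction power is an illustration on the sample-size scale.

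**The case against.** The other side has several good points, and they set the limits of this one.

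- A reader might infer that every endpoint will be re-tested within types at the full 0.05 level, and that chance differences will be presented as real. The article says neither. It gives no level for the subgroups and announces no claim from them.
- A reader might infer that CM patients sit in both subgroups. That follows only if the slash means 'and'. If it means 'versus', CM is the common comparator in two alternative splits and nothing overlaps. The defect is then an unfixed choice.
- The absence of a multiplicity rule, an exploratory label or a named interaction test may be made good in a full protocol or SAP that is not shown. Absence alone is no finding.
- A reader might infer that a null trial would probably produce a positive subgroup. Counting time points and both HIT-6 forms gives 1 + 2 + 2 + 4 + 2 + 1 + 2 + 2 = 16 comparisons. Simulating these in two types with no true effect gives at least one P < 0.05 in about 61% of trials at an assumed correlation of 0.5. That count is two-sided: a result favouring gastrodin arises in about 34% (43% at correlation 0.3, 25% at 0.7). The stronger statement is not supported.
- There is a single subgroup factor, declared in advance with a rationale. The diagnosis is recorded at baseline (Table 3), and the Blinding section keeps the statistician blinded until analyses are finished. This narrows the room for a data-driven choice but does not remove it, because the choice between the two splits stays open.

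What remains is what the article does state: a grouping that offers two splits, and tests that do not answer the question posed.

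**Conclusion.** The point holds in limited form. The article defines the subgroups rather than leaving them to another document, and the definition does not give one partition. The group-comparison tests it names do not address its stated question about headache type. If within-type P values were used to answer that question, they would disagree in about 47% to 54% of trials with identical true effects. This assumes 90% overall power and a split between 50:50 and 70:30; a more uneven split makes it worse. The documents do not show that results will be read this way, so the figure measures a risk to be closed off and not an error already committed. The primary comparison does not depend on the subgroup analysis. Severity is minor.

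**What to change.** Before unblinding:

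1. Name one non-overlapping partition based on the pre-existing headache diagnosis already collected at baseline, for example CM versus not CM, and drop the alternative.
2. For the primary endpoint, fit a model with treatment, headache type and their interaction, and report the interaction estimate with its 95% CI.
3. Show the within-type effects for all endpoints as exploratory estimates with CIs, and base no efficacy claim on a within-type P value.

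The cost is about one rewritten sentence and one model term, with no new data. The price is low power: about 36–40% to detect 24 points in one type against 0 in the other. A non-significant interaction must therefore not be read as proof that the effect is the same in both types, and the CI should carry the interpretation.
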